#### Key Secondary Outcome Measures

Key secondary outcomes will be the change from baseline to 12 weeks in each of the four individual items comprising the 4-item heart attack response preparedness score. These item-level analyses will be conducted as prespecified key secondary endpoints to characterize which components of the summary score are most affected by the intervention.

#### Secondary Outcome Measures

To evaluate user perceptions of the HeartBot II intervention, we will include several validated and study-developed measures that assess chatbot communication quality, message perception, and user attitudes toward AI in health.

#### HeartBot II Message Effectiveness

Message effectiveness will be assessed using the effectiveness scale [33,34], which consists of five semantic differential items (effective—ineffective, helpful—unhelpful, beneficial—not beneficial, adequate—not adequate, supportive—not supportive). Each item will be rated on a 7-point scale, with 1 indicating the negative pole and 7 indicating the positive pole. Scores will be averaged to create a composite score, with higher values indicating greater perceived message effectiveness.

#### Impression of Chatbot Messages

Perceived humanness of chatbot messages will be measured using the anthropomorphism scale [35], consisting of five bipolar adjective pairs: (fake—natural, machinelike—humanlike, unconscious—conscious, artificial—lifelike, rigid—adaptive). Items will be rated on a 7-point scale, and scores will be averaged to compute a composite humanness score, where higher scores reflect more mechanical impressions of the chatbot.

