#### Conversational Naturalness and Coherence

Two single-item measures will assess perceived conversational quality: “Overall, how would you rate the conversations with your texting partner?” (1=Very unnatural to 5=Very natural), “Overall, how would you rate the messages you received?” (1=Very incoherent to 5=Very coherent).

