#### Multiplicity and Gatekeeping Procedure

To control the family-wise error rate, a hierarchical gatekeeping procedure will be used for the primary and key secondary outcomes. First, the group-by-time interaction for the heart attack response preparedness score will be tested at a two-sided alpha level of 0.05. Only if the primary outcome is statistically significant will the four individual component items be formally tested as key secondary outcomes. *P* values for the four key secondary outcomes will be adjusted using the Holm-Bonferroni step-down procedure. All other secondary outcomes will be treated as exploratory; analyses will be descriptive or inferential, as appropriate, with nominal p-values reported without adjustment for multiplicity.

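### The chatbot humanness score is named in one direction and interpreted in the other, and its 1 and 7 anchors are not given

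*Protocol article*

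**What the plan says.** The section Impression of Chatbot Messages gives the construct first: "Perceived humanness of chatbot messages will be measured using the anthropomorphism scale". The five pairs are "fake—natural, machinelike—humanlike, unconscious—conscious, artificial—lifelike, rigid—adaptive". On response format it says only "Items will be rated on a 7-point scale", and the composite rule is that "scores will be averaged to compute a composite humanness score, where higher scores reflect more mechanical impressions of the chatbot".

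Two neighbouring sections show how similar measures are scored. HeartBot II Message Effectiveness is also a five-item, 7-point semantic differential. It fixes its anchors, "with 1 indicating the negative pole and 7 indicating the positive pole", and its composite runs "with higher values indicating greater perceived message effectiveness". Conversational Naturalness and Coherence scores its naturalness item "1=Very unnatural to 5=Very natural".

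On the status of the outcome, Multiplicity and Gatekeeping Procedure says: "All other secondary outcomes will be treated as exploratory".

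**The concern.** The construct and the name of the composite both say that more means more human. The interpretation clause says that more means more mechanical. No reverse-coding step links the two, and nothing elsewhere in the article settles which is intended.

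A more human-like conversation is one of the reasons the Introduction gives for moving from the rule-based HeartBot I to a large language model. This composite is the multi-item measure of that quality. An analyst who follows the interpretation clause and one who follows the score's name would draw opposite conclusions from the same data. A reader of the results could not tell which had been done. If the direction is settled only after the ratings have been seen, it becomes a post hoc choice.

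**Working it through.** The plan has no sample size, power or alpha figure that depends on this point, so there is no figure to reproduce. The check applies the stated rule to clear-cut respondents under both possible codings.

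**Inputs**
- From Impression of Chatbot Messages: five items, each rated 1 to 7; an unweighted mean; higher is to be read as more mechanical; the score is called humanness.
- Pole order in the same section: all five pairs put the mechanical word first and the human word second, so there is no mixed keying.
- Not given there: which pole is 1 and which is 7. Both codings are therefore tried.

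**Formula.** S = (x1 + x2 + x3 + x4 + x5) / 5, with S between 1 and 7. Reversing the key turns S into 8 − S.

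**Coding A: 1 = mechanical pole, 7 = human pole**
- Respondent choosing the human pole throughout: S = (7+7+7+7+7)/5 = 7. The stated rule reads this as most mechanical, the opposite of the answers.
- Respondent choosing the mechanical pole throughout: S = (1+1+1+1+1)/5 = 1. The stated rule reads this as least mechanical, again the opposite.
- Group mean of 6: close to the human end, but read as mechanical. On a score that really did rise with mechanical impressions, the same answers would give 8 − 6 = 2.
- Result: the name is right and the interpretation is reversed.

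**Coding B: 1 = human pole, 7 = mechanical pole**
- Human pole throughout: S = 1, correctly read as least mechanical.
- Mechanical pole throughout: S = 7, correctly read as most mechanical.
- Result: the interpretation is right, but the humanness score is lowest for the most human-like rating, so the name is wrong.

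Name and stated direction do not agree under either coding.

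**Which coding is likelier**
- Print order does not decide it. Message Effectiveness prints the favourable word first in each pair and still scores the favourable pole 7, so in this article the order of the words is not the order of the numbers.
- The scoring convention is better evidence. Message Effectiveness gives 1 to the negative pole and 7 to the positive pole, and the naturalness item also rises with the favourable quality. Carried over to this scale, with human taken as the favourable pole, that gives Coding A. This is an inference, because the convention is stated only for those other measures.

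**The case against.** The strongest reply is that a sign reversal has not been shown. It needs 7 to be the human pole, and the section does not print that. Under the other keying every result would be read correctly and only the label would need changing. This stands. A reader might infer from the order of the adjectives that the trial will report a human-like chatbot as mechanical. The article does not support that as a certainty, because the adjacent scale shows that print order and numeric coding can run in opposite directions.

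A second reply is that a journal article commonly leaves item anchors to the full protocol. That is fair for the anchors alone, and their absence would not be a finding by itself. It does not answer the contradiction, because the article makes a positive statement of direction that conflicts with the name in the same sentence. A fuller document could show which half is wrong but could not make both right.

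A third reply concerns importance, and most of it stands:
- The outcome is exploratory.
- A reader might take this score as the only test of whether the language model made the chatbot seem human. It is not. Naturalness has its own anchored item, and Chatbot Identity Perception asks whether the partner seemed human or AI. A reversed composite would probably show up as a conflict with those items.
- The waitlist group does not use HeartBot II before week 12, so this score supports no meaningful randomized comparison at that time.
- The item ratings are collected in REDCap, so the direction can be corrected later without loss of data.

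**Conclusion.** The point holds as a contradiction in a stated scoring rule: the composite's name and its stated direction cannot both be right, and the article gives no anchors to show which is wrong.

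The consequence depends on the coding. If 7 is the human pole, the stated interpretation reverses the result completely, so that S is read as 8 − S should be. If 7 is the mechanical pole, no result is reversed and the score is misnamed. The first is more likely, given how the neighbouring measures are scored, but that rests on carrying their convention over to this scale.

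Severity is minor to moderate. The error affects one exploratory secondary outcome. The preparedness score, the four key secondary items, the gatekeeping procedure and the sample size do not depend on it.

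**What to change.** Before the week-12 data are analysed:

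1. Look up in REDCap which pole carries 1 and which carries 7 for each of the five items, and state it in the section.
2. Make name and direction agree. The preferred form keeps the name and matches the neighbouring scales: 1 = mechanical pole, 7 = human pole, items averaged, higher scores meaning a more human-like impression.
3. If REDCap is keyed the other way, reverse-code each item as 8 − x when the score is derived, and say so. Leave the form on screen unchanged, so that every participant answers the same version.

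The REDCap check should come first, because new wording that presumed the coding could introduce the error it is meant to remove.

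The cost is one corrected sentence and a short coding check, with no new data and no change to any other analysis. Enrollment began in April 2026, so the first 12-week surveys fall due from about late June 2026. Settling the direction before those ratings are examined avoids a post hoc choice.

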#### Conversational Naturalness and Coherence

Two single-item measures will assess perceived conversational quality: “Overall, how would you rate the conversations with your texting partner?” (1=Very unnatural to 5=Very natural), “Overall, how would you rate the messages you received?” (1=Very incoherent to 5=Very coherent).

#### Chatbot Identity Perception

Participants will be asked to identify who they believe they interacted with during the intervention: “Do you think you texted a human or artificial intelligent chatbot during your conversation?*”* with two response options: (1) human and (2) AI chatbot.

#### AI Attitudes in Health Context

To explore perceptions of AI in health care, participants will be asked to rate agreement with the following three statements using a 5-point Likert scale (1=Strongly disagree, 5=Strongly agree): “The use of artificial intelligence will result in better healthcare,”“The use of artificial intelligence will result in better health outcomes,” “Artificial intelligence may help me reduce my risk of heart disease.”

### Other Measures

#### Perceived Risk of Heart Attack

Perceived susceptibility will be assessed using three items asking participants to compare their risk of experiencing a heart attack to other women their age over different time frames (next 5 y, next 10 y, lifetime). Responses will be measured on a 5-point Likert scale from “Very unlikely” to “Very likely.”

#### Sociodemographic and Health Risk Factors

Basic demographic information, including age, race and ethnicity, education, income, marital status, and employment status will be self-reported. Cardiovascular risk factors will also be assessed, including smoking status, current use of prescribed blood pressure, cholesterol, or diabetes medication, and family history of heart disease. These items were selected based on current clinical guidelines [36].

#### Multiplicity and Gatekeeping Procedure

To control the family-wise error rate, a hierarchical gatekeeping procedure will be used for the primary and key secondary outcomes. First, the group-by-time interaction for the heart attack response preparedness score will be tested at a two-sided alpha level of 0.05. Only if the primary outcome is statistically significant will the four individual component items be formally tested as key secondary outcomes. *P* values for the four key secondary outcomes will be adjusted using the Holm-Bonferroni step-down procedure. All other secondary outcomes will be treated as exploratory; analyses will be descriptive or inferential, as appropriate, with nominal p-values reported without adjustment for multiplicity.

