#### Primary Outcome Measures

The primary outcome will be change from baseline to 12 weeks in a 4-item heart attack response preparedness score, calculated as the mean of four items assessing confidence in (1) recognizing heart attack symptoms, (2) distinguishing heart attack symptoms from other medical problems, (3) calling 911 or an ambulance if a heart attack is suspected, and (4) reaching an emergency department within 60 minutes of onset. The measure has been adapted from a previously validated scale [28,29], which has been used in prior studies with diverse samples of women to support generalizability [30-32]. Participants will answer the following four questions on a 4-point scale, ranging from 1, in which 1 indicates “not sure,” to 4, which indicates “sure”: (1) How sure are you that you could recognize the signs and symptoms of a heart attack in yourself? (2) How sure are you that you could tell the difference between the signs or symptoms of a heart attack and other medical problems? (3) How sure are you that you could call an ambulance or dial 911 if you thought you were having a heart attack? (4) How sure are you that you could get to an emergency room within 60 minutes after the onset of your symptoms? All items are self-reported and collected online. In pilot data [18], the 4-item scale demonstrated acceptable internal consistency (Cronbach α=0.70).

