#### Statistical Analysis

Baseline characteristics will be summarized by randomized group using counts and percentages for categorical variables and means and standard deviations for continuous variables, or medians and interquartile ranges for skewed variables. Because treatment assignment is randomized, baseline characteristics will be described primarily to assess sample comparability rather than to guide significance-based inference.

Primary efficacy analyses will compare randomized groups from baseline to 12 weeks, before the waitlist group receives the intervention. The treatment effect for the primary outcome, a 4-item heart attack response preparedness score, will be estimated using constrained longitudinal data analysis (cLDA) implemented via linear mixed models (LMMs) [37]. Consistent with the randomized design, the models will constrain the mean scores for the treatment and control groups to be equal at baseline. The primary outcome will include categorical fixed effects for time and a time-by-treatment group interaction term. The primary model contrast of interest is the coefficient for this interaction term at the 12-week follow-up, representing the baseline-adjusted between-group difference. To account for the within-subject correlation between baseline and follow-up, the cLDA models will use an unstructured covariance matrix, allowing variances and correlations to differ over time.

The 4 individual preparedness items will be analyzed as prespecified key secondary outcomes, subject to the hierarchical gatekeeping procedure described above. The primary efficacy analysis and all key secondary analyses will be based on the baseline and 12-week assessments only. Although the individual items are ordinal, the primary analysis will use the same linear cLDA framework to facilitate interpretation of mean differences and support model stability [38]. Robustness of this linear approximation will be evaluated in sensitivity analysis using ordinal logistic mixed-effects models for each individual item.

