#### Power and Sample Size

This study is powered based on a total analyzed sample of n=160 (80 per group). To account for a conservative 20% attrition, we will enroll a total of 200 participants. Statistical power was estimated via Monte Carlo simulations (5000 iterations) using an empirical covariance matrix and response thresholds derived from pilot data [18]; code is provided in Multimedia Appendix 1. The simulation uses the same cLDA analysis framework described above for analysis.

For the primary outcome, the heart attack response preparedness score, the study provides 90% power to detect a raw mean difference of 0.37 points on the 1‐4 scale (Cohen *d*=0.51). This detectable effect is smaller than the within-group mean change observed in pilot data (0.78 points), although the pilot study did not include a control group [18]. For the four key secondary item-level outcomes, power was also evaluated under the prescribed hierarchical gatekeeping procedure with Holm-Bonferroni adjustment. Under this framework, the study has 90% power to detect at least one significant key secondary item for a raw difference of 0.43 (*d*=0.59). To detect significant effects across all four key secondary items (assumed to have the same effect), larger effect sizes are required; 90% power is achieved at a mean difference of 0.62 points (*d*=0.85).

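### Behind the composite-score gate, Holm's first step of 0.05/4 on the four items is stricter than 5% family-wise control needs; starting at 0.05/3 gives a small, free gain in power

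*Protocol article*

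**What the plan says.** All of this is in the Methods of the protocol article.

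- **Gate** (Multiplicity and Gatekeeping Procedure): "the group-by-time interaction for the heart attack response preparedness score will be tested at a two-sided alpha level of 0.05". Then: "Only if the primary outcome is statistically significant will the four individual component items be formally tested as key secondary outcomes".
- **Item tests** (same section): P "values for the four key secondary outcomes will be adjusted using the Holm-Bonferroni step-down procedure". With four items the thresholds are 0.05/4, 0.05/3, 0.05/2 and 0.05.
- **Primary outcome** (Primary Outcome Measures): the score is "calculated as the mean of four items assessing confidence in" four aspects of heart attack response.
- **Key secondary outcomes** (Key Secondary Outcome Measures): "the change from baseline to 12 weeks in each of the four individual items comprising the 4-item heart attack response preparedness score".
- **Item model** (Statistical Analysis): for the items, "the primary analysis will use the same linear cLDA framework to facilitate interpretation of mean differences and support model stability".
- **Power** (Power and Sample Size): 90% for the score at 0.37 points (d = 0.51) with 80 analysed per group. For the items: "Under this framework, the study has 90% power to detect at least one significant key secondary item for a raw difference of 0.43" (d = 0.59), and 90% power for all four items at 0.62 (d = 0.85).

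**The concern.** A four-way Holm correction protects against any number of true item nulls, from one to four. Its first threshold, 0.05/4 = 0.0125, is needed only when all four are true. Here that configuration is part of the primary null, because the score is the exact mean of the items and both levels compare means in the same linear model. A trial in which nothing works must first pass the gate falsely before any item can be claimed, and the gate allows that at most 5% of the time. The divisor of 4 therefore guards a second time against a case already covered.

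At stake is the chance of naming at least one component after a significant score. The trial can end with a significant score and no item that can be claimed, and a first threshold of 0.0125 makes that somewhat more likely than it needs to be.

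**Working it through.** **Inputs.** 80 per group; gate at two-sided 0.05; score difference 0.37 with d = 0.51; Cronbach alpha 0.70 (Primary Outcome Measures). The pilot covariance matrix is not shown, so these are inferred:

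- Score SD: 0.37/0.51 = 0.725.
- Mean inter-item correlation from alpha with four items: r = 0.70/(4 − 3 × 0.70) = 0.368.
- Item SD, with equal variances and correlations: 0.725/√((1 + 3 × 0.368)/4) = 0.725/0.7255 = 1.00.

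**The plan's own figures first.** Items were simulated as multivariate normal, with the gate and then Holm.

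| Quantity | Plan | Recomputed |
|---|---|---|
| Enrolment, 160/(1 − 0.20) | 200 | 200 |
| Score power at 0.37 | 90% | 89.7% |
| At least one item at 0.43 | 90% | 89.4% |
| All four items at 0.62 | 90% | 91.0% |

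The power section is reproduced closely under gate plus Holm.

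**A conflict over the item SD.** The printed item effect sizes imply a smaller SD: 0.43/0.59 = 0.729 and 0.62/0.85 = 0.729, close to the score SD of 0.725. With 0.729 as the item SD, power for at least one item at 0.43 would be 99.5%, not 90%. An item SD near 1.00 is the reading that reproduces the printed power, so it is used below.

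**Error control with thresholds 0.05/3, 0.05/3, 0.05/2, 0.05.**

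1. *Primary null true.* This includes all four item nulls, and effects that cancel. Any false claim needs a false gate pass, with probability at most 0.05 whatever the item thresholds.
2. *Primary null false.* At least one item effect is non-zero, so k, the number of true item nulls, is at most 3. Before the first false rejection at most 4 − k items have been rejected, so it occurs at step 5 − k or earlier. The threshold there is at most 0.05/k: step 2 gives 0.05/3 for k = 3, step 3 gives 0.05/2 for k = 2, step 4 gives 0.05 for k = 1. Bonferroni over k true nulls gives at most k × 0.05/k = 0.05.

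The two cases are exhaustive. The argument needs valid individual tests and linked estimands, and makes no assumption about correlation.

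**Simulated item-level family-wise error, Holm versus modified:** all four null, 2.3% vs 2.8%; one very large effect and three nulls, 4.7% vs 4.7%; three very large effects and one null, 5.0% vs 5.0%; two opposite effects with a null score, 2.1% vs 2.1%.

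**Power, Holm versus modified** (equal effects, SD 1.00, r = 0.368):

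| Quantity | Holm | Modified |
|---|---|---|
| At least one item at 0.37 | 77.6% | 80.7% |
| At least one item at 0.43 | 89.4% | 91.3% |
| Average per item at 0.43 | 68.0% | 68.6% |
| All four items at 0.62 | 91.0% | 91.0% |
| Difference giving 90% for at least one item | about 0.43 | about 0.42 |

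A significant score with no claimable item, at 0.37, goes from 89.7 − 77.6 = 12.1% to 89.7 − 80.7 = 9.0%.

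**Sensitivity.** At 0.43 the gain is 1.3 points for r = 0.60 and 3.0 points for r = 0.20. With an item SD of 0.73 it is 99.5% to 99.6%. With unequal effects of 0.60/0.50/0.30/0.08 (mean 0.37) it is 88.8% to 89.2%. With 0.9/0.6/0/0 it is zero.

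**The case against.** The strongest reply is that nothing here is wrong. Gate plus Holm is a complete, prespecified procedure that controls the family-wise error, and the power section describes it accurately. The gain comes only when the smallest item p-value falls between 0.0125 and 0.0167. The items are meant to show which components respond most, which anticipates unequal effects, and there the gain shrinks to 0 to 0.4 points. At the pilot's uncontrolled change of 0.78, power for at least one item is above 99.99% under either rule. The size rests on an inferred item SD that conflicts with the printed item d. And 86 participants were already enrolled by June 2, 2026, in a trial whose participants know their assignment.

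Most of this stands, and it limits the importance of the point. It does not defend the divisor of 4, since the alternative rejects everything Holm rejects with the same error guarantee. Item-level error under the complete null does rise, from 2.3% to 2.8%. In that case, however, every false item claim accompanies a false score claim, so the error over score and items together is the gate's 5% under both rules.

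A reader might infer that the written rule inflates error or contradicts the power section. It does neither. Nor are the items the trial's only confirmatory result: the score is itself confirmatory, and item estimates can be reported whatever the tests show.

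**Conclusion.** The point holds as a small, free efficiency improvement. The written procedure is valid, and its first item threshold is stricter than 5% family-wise control requires. The error-control argument is exact for the linear cLDA item tests; it does not extend to the ordinal sensitivity models.

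The size is less certain. It assumes equal item effects, an item SD near 1.00 and r near 0.37, inferred from alpha and the score's d. On that basis power for at least one item rises by about 2 points at 0.43 and about 3 points at 0.37. The gain is never negative. A reader might conclude that the trial is giving up substantial power. The figures do not support that: the gain is near zero with strongly unequal effects or an item SD near 0.73, and nil for all four items. The primary test, its power and the sample size are unaffected.

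**What to change.** In Multiplicity and Gatekeeping Procedure, replace the Holm sentence with wording such as: if the primary null is rejected, the ordered item p-values p(1) to p(4) from the linear cLDA models are compared step-down with 0.05/3, 0.05/3, 0.05/2 and 0.05 (Shaffer-modified Holm, valid because the four item nulls together imply the primary null). Adjusted p-values are the running maximum of 3p(1), 3p(2), 2p(3) and p(4), and are not less than the primary p-value.

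Then change the first threshold in the Multimedia Appendix 1 code, re-run it with the pilot covariance, and restate the figure for at least one item (about 0.42 on the assumptions above). State at the same time which SD the printed item d values use. The figure for all four items should not move.

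The cost is a dated amendment and a one-line justification of a less familiar rule. It needs no added participants, data or modelling assumptions. It should be made before anyone sees outcome data by arm, which is feasible with analysis expected in spring 2027.
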